**Methods:**

A mixed methods pilot trial will be conducted in Côte d’Ivoire and will consist of 3 phases: (1) the development and improvement of the eSkinHealth app, (2) a pilot trial to evaluate the usability of the eSkinHealth app for local medical staff in Côte d’Ivoire, and (3) a pilot trial to evaluate the effectiveness of early detection and case management of targeted skin NTDs (Buruli ulcer, leprosy, yaws, and lymphatic filariasis) with the eSkinHealth app in Côte d’Ivoire. The pilot study will be implemented as a 2-arm trial with local health care providers and patients with skin NTDs over a 3-month follow-up period. The local health care providers will be assigned to an intervention group receiving the eSkinHealth app to be used in their daily practices or a control group. Training will be provided on the use and implementation of the app and the diagnostic pipeline to the intervention group only, while both groups will receive training on skin diseases. Our primary outcome is to evaluate the early detection and effective management of skin diseases using the eSkinHealth app in Côte d’Ivoire by the number of cases diagnosed and managed. Additionally, we will evaluate the eSkinHealth app with validated questionnaires and in-depth interviews. Procedures of our methods have been reviewed and approved by the Institutional Review Board of the Ministry of Health, Côte d’Ivoire and by Tulane University in 2021.

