### Recruitment Procedure

We will select 10 to 12 PHCs in health districts with multiple skin NTDs coendemicity as our study site and allocate them equally into intervention and control arms. Targeted patients will include individuals with skin diseases identified through skin surveillance activities and who access the selected PHCs for diagnosis and treatment of their conditions. Local health care providers will be recruited purposively from our study site. A total of 44 local health care providers, including nurses and community health workers, will be selected to participate in the study; the number per PHC will be based on the population of the catchment area of the PHC. All participants will be enrolled formally only after signing the informed consent form.

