### Statistical Analysis

#### Sample Size Estimation

As for patients, a convenience sample (N=1320) of participants eligible to participate in this pilot study will be recruited. Sample size calculations were not conducted, as this is a pilot trial. The sample size of 1320 was selected based on the number of participants that could be conveniently recruited and tested within the pilot study time frame. From our previous studies, the average number of patients that got registered to the eSkinHealth app was approximately 10 per PHCs per month.

As for local health care providers, 44 local health care providers (22 local health care providers per group) will be recruited for this study. A power analysis was performed using G*Power 3.1.9.6. An estimated medium effect size of Cohen *f* 0.25 was used to determine the sample size needed for a repeated-measures multivariate analysis of variance (RMANOVA) with three time points and two groups. With 95% power (1 – ß), a sample size of 44 local health care providers is needed to detect the hypothesized medium-sized effects on the various outcomes. This RMANOVA would uncover all large- and medium-sized effects but no small-sized effects.

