#### Data Analysis

Statistical analyses will be performed using Stata software (version 16, StataCorp). The threshold for statistical analyses will be set at *P*<.05 in a 2-tailed test. We will summarize the baseline data by group assignment using descriptive statistics: means and SDs will be used for continuous data with normal distribution, medians and IQRs for skewed data, and percentages for categorical data. Our primary outcome, number of diagnosed and early detection will be assessed by mix model analysis of variance, with intervention assignment as a between-group factor and time as a within-subject factor. As for continuous data, we will compare the data between control and intervention group using the *t* test or the Wilcoxon Mann-Whitney test. For categorical data, we will compare the data using the chi-square test.

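### Health centres are allocated to the arms, but no named analysis has a health-centre level and the subject of the mixed ANOVA is undefined; patient-level tests would not hold the 5% level

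*Protocol article*

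**What the plan says.** In the protocol article, Recruitment Procedure makes the PHC the unit of allocation: "We will select 10 to 12 PHCs in health districts with multiple skin NTDs coendemicity", and the plan is to "allocate them equally into intervention and control arms". Providers are then recruited from those centres, and "the number per PHC will be based on the population of the catchment area of the PHC". The Methods paragraph of the Abstract words it differently: "The local health care providers will be assigned to an intervention group receiving the eSkinHealth app to be used in their daily practices or a" (the sentence then names the comparison arm).

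Data Analysis sets a two-sided 5% threshold. The primary outcome goes into a mixed-model ANOVA "with intervention assignment as a between-group factor and time as a within-subject factor". Continuous data are compared between arms by t test or Wilcoxon Mann-Whitney test, and "For categorical data, we will compare the data using the chi-square test". Neither sentence names an outcome or a unit of analysis.

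Sample Size Estimation bears on cluster size in two ways: "a convenience sample (N=1320) of participants eligible to participate in this pilot study will be recruited", and "the average number of patients that got registered to the eSkinHealth app was approximately 10 per PHCs per month". It also states 95% power for 44 providers in a design with two groups and three time points. No cluster term, ICC, design effect or robust variance appears in the article.

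**The concern.** Patients and providers at one PHC share staff, catchment and local endemicity, so their outcomes are likely to be correlated. When whole PHCs are allocated, the arm comparison rests on 5 to 6 independent units per arm. The t, Wilcoxon and chi-square tests assume independent observations, as does a mixed ANOVA with only group and time unless its subject is the PHC itself. Any positive ICC then makes the standard errors too small and the P values too low.

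This is more than detail left to an analysis plan. The article names tests that do not match its own unit of allocation, and a plan that followed the text would carry the mismatch forward. The trial is a pilot, but it applies a significance threshold, and its Discussion promises evidence of effectiveness for policy makers.

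**Working it through.** **The plan's own figure.** The inputs stated in Sample Size Estimation are f = 0.25, 2 groups, 3 time points, 95% power and N = 44; alpha 0.05 comes from Data Analysis. Assumed, because not stated: correlation 0.5 between time points and sphericity.

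- Group-by-time interaction: lambda = N × m × f² / (1 − rho) = 44 × 3 × 0.0625 / 0.5 = 16.5, with df 2 and 2 × (44 − 2) = 84. Power is 95.6%, and 44 is the smallest even N that reaches 95%.
- The multivariate version gives 46 (94.8% at 44).
- The between-group main effect would need 142 and has 51% power at 44.

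So 44 reproduces as an interaction test on independent providers.

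**Patient-level tests.** Cluster size n is 1320 / 12 = 110 or 1320 / 10 = 132 from the stated total, and 10 × 3 = 30 from the stated monthly rate over 3 months. The ICC is assumed. Design effect DE = 1 + (n − 1) × ICC; true type I error = 2 × (1 − Phi(1.96 / √DE)).

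| Patients per PHC | ICC 0.01 | ICC 0.05 | ICC 0.10 |
|---|---|---|---|
| 30: DE | 1.29 | 2.45 | 3.90 |
| 30: type I error | 8.4% | 21.1% | 32.1% |
| 110: DE | 2.09 | 6.45 | 11.9 |
| 110: type I error | 17.5% | 44.0% | 57.0% |
| 132: DE | 2.31 | 7.55 | 14.1 |
| 132: type I error | 19.7% | 47.6% | 60.2% |

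A beta-binomial simulation (20,000 runs, event rate 30%) of the chi-square test with 12 PHCs gave 8.5/21.1/32.4% at 30 per PHC and 17.6/44.5/57.7% at 110. A t test on the PHC proportions from the same simulated data stayed between 4.8% and 5.2%. At ICC 0.05 the effective sample size is 1320 / 6.45 = 205 with 110 per PHC, and 360 / 2.45 = 147 with 30 per PHC (360 = 12 × 30).

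**Mixed ANOVA of case counts.** The result depends on the undefined subject.

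- Subject is the PHC: the analysis is already at cluster level, and simulated type I error is about 5%.
- Subject is the provider (44 / 12 = 3.7 to 44 / 10 = 4.4 per PHC), PHC ignored: simulated type I error is 6 to 7% at ICC 0.05, 9 to 11% at 0.10 and 12 to 18% at 0.20.

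**Power with clustering.** Divide lambda by DE and use PHC-level df of 2 and 2 × (J − 2), that is 16 for J = 10 PHCs and 20 for J = 12.

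| ICC | DE, 12 to 10 PHCs | Power, 10 to 12 PHCs | Providers at 44 × DE |
|---|---|---|---|
| 0.05 | 1.13 to 1.17 | 87 to 90% | 50 to 52 |
| 0.10 | 1.27 to 1.34 | 82 to 86% | 56 to 59 |
| 0.20 | 1.53 to 1.68 | 72 to 78% | 68 to 74 |

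One condition applies to the interaction. A PHC effect that is constant over time cancels out of it, so these power figures take the ICC to describe providers' changes over time.

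**The case against.** The strongest reply concerns scope. The primary outcome is chiefly a number of cases, which is not a patient-level variable; its natural subject is a provider or a PHC. The large error rates above are for patient-level tests and do not transfer to it. This stands. A reader might infer that every planned analysis, the mixed ANOVA included, is far too optimistic. The document does not support that: with the PHC as subject there is no inflation, and with about four providers per PHC it is modest.

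The unit for the t, Wilcoxon and chi-square tests is also inferred. Data Analysis names none, so the patient-level figures are conditional on that use. If early detection is analysed as a proportion of patients, it is exposed to them; the text does not fix its unit.

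A reader might also conclude that a false claim of benefit is likely. The rates do not show that. They hold only when there is no true effect and rest on an assumed ICC, and at 30 or 110 patients per PHC only one of the six exceeds 50%. The cluster size is unsettled as well, since the stated total and the stated monthly rate point to different values.

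Finally, the article plans P values and names no confidence intervals; wider intervals follow only because the same standard errors would be used. The pilot label explains why there is no patient sample-size calculation. It does not make P values valid when the allocated unit is ignored.

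**Conclusion.** The point holds in this form: PHCs are allocated, no named analysis has a PHC level, and the subject of the mixed model is undefined. The direction of the error is certain for any positive ICC whenever the unit analysed lies below the PHC and the PHC effect enters the comparison. Its size depends on which unit is analysed and on an ICC that the article does not give.

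For patient-level tests the departure is serious even at the lowest assumed ICC of 0.01: about 8% with 30 patients per PHC and 18% with 110. For provider-level case counts it is mild to moderate, and for PHC-level counts it is nil. The stated 95% power is arithmetically right for independent providers and too favourable if providers within a PHC are correlated in the quantity tested.

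**What to change.** 1. Name the PHC as the unit of allocation and reconcile the Abstract with Recruitment Procedure.
2. Define the subject of the mixed model, and state the unit of analysis for each outcome, including early detection.
3. Replace tests that treat patients or providers as independent by one of two approaches:
   - PHC-level summaries compared by a t test with 8 to 10 df (10 − 2 to 12 − 2), with case counts expressed as rates per catchment population. A permutation test is justified only if PHCs were randomised; the article says allocated and does not mention randomisation.
   - Mixed models with a random PHC intercept, and provider nested in PHC for repeated measures. Use small-sample degrees of freedom (Kenward-Roger or Satterthwaite) for continuous outcomes. Use a logistic or count model with a small-sample correction for binary outcomes and counts.
4. Restate the power for 44 providers with the clustering assumption made explicit, over a range of ICCs.

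Recruitment need not change, and data collection need not either provided the PHC is recorded for every patient and provider and catchment populations are available. The cost is larger P values, wider intervals and a less favourable stated power.

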### Ethics Approval

Procedures of our methods have been reviewed and approved by the IRB of the Ministry of Health, Côte d’Ivoire (No. IRB000111917) and by the Tulane University (IRB 2020-2054-SPHTM). This study is registered at ClinicalTrials.gov (NCT05300399).

## Results

This study was funded in 2021. We started the enrollment of patients in February 2022, and data collection is currently underway. Data collection is expected to be completed in October 2022. We expect the first results to be submitted for publication in 2023.

## Discussion

This paper outlines the protocol for a 3-month pilot trial for evaluating the effect of the eSkinHealth app for the early detection and management of skin NTDs. This app has been our invention, and to our knowledge, there is no other mHealth app of this kind that is developed for the collection of the clinical data of skin diseases in which it can be used both online and offline. It is also portable, and therefore, it can be used in remote communities in LMICs where skin NTDs are endemic and where infrastructure is usually very poor. In terms of teledermatology, while past attempts in using WhatsApp and other social media platforms have shown successful results to an extent [20,21], they do not offer patient health information security. Furthermore, information is exchanged on a one-time basis, and it does not offer a platform for the follow-up of patients. Our system attempts to overcome these challenges.

The outcomes of this study will be primarily assessed by the number of cases of skin NTDs diagnosed and managed using the eSkinHealth app in Côte d’Ivoire, consistent with previous studies in LMICs [30-34]. We will further evaluate it with the SUS score and in-depth interviews. We expect that the average SUS score will be above 68, and the usability of the eSkinHealth app would be considered above average. We hypothesize that the use of the eSkinHealth app will improve the early detection and management of skin NTDs.

Our study may have several limitations. First, although the app can be used offline, an internet connection is required for certain functions. Poor internet connectivity may affect our results. While we can exclude PHCs with known poor internet connectivity, this will form one of the results of our study. We therefore did not include this as our criteria in the selection of the users. Second, the SUS will be evaluated at enrollment, the midpoint (week 6), and the end point (week 12). It is unclear what the effects of the intervention would be if it were prolonged. Lastly, this is a pilot trial involving 10 to 12 PHCs in one or two health districts, and therefore, the study findings may not be generalizable to all health districts in Côte d’Ivoire. These limitations notwithstanding, this study is the first to examine the usability and the effectiveness of the eSkinHealth app to improve the early detection and case management of skin NTDs in Côte d’Ivoire.

The study will provide robust evidence of the usability and the effectiveness of the eSkinHealth app to improve the early detection and case management of skin NTDs in Côte d’Ivoire. Furthermore, given the importance of improving the early detection and case management of skin NTDs in LMICs, these results will provide a compelling rationale for infectious disease policy and decision makers regarding mHealth interventions for skin NTDs in LMICs.

## Appendix

Multimedia Appendix 1 Peer review report from the Center for Scientific Review Special Emphasis Panel - Mobile Health: Technology and Outcomes in Low and Middle Income Countries (National Institutes of Health, USA).

## Abbreviations

IRB: institutional review board
LMICs: low- and middle-income countries
mHealth: mobile health
NTD: neglected tropical disease
PHC: primary health center or clinic
RMANOVA: repeated-measures multivariate analysis of variance
S3: Simple Storage Service
SUS: System Usability Scale
